## Methods

### Study design and setting

This observational prospective pilot study will be conducted in New York City Health + Hospital (NYC H+H)/Jacobi, New York, United States of America affiliated to Albert Einstein College of Medicine and Laikon General Hospital, Athens, Greece affiliated to National and Kapodistrian University of Athens. The study has been reviewed and approved from Biomedical Research Alliance of New York (BRANY) and the respective NYC H+H committee, as well as the ethics committee of Laikon General Hospital. Verbal informed consent will be obtained from all participants. Written consent was waived as POCUS is the standard of care and an integral part of physical examination in modern clinical medicine.

### Population, Inclusion and Exclusion Criteria

We plan to include 120 men and women (at least 20 of them from the Laikon site) with the inclusion criteria consisting of patients ≥50 years of age, who undergo preoperative medical assessment for a major abdominal surgery under general anesthesia, have RCRI ≥2 (moderate or higher risk), and ASA-PS: II, III, IV (Table 1 and 2).

**Table 1. T1:** Revised Cardiac Risk Index (RCRI) for preoperative risk

RCRI clinical variable	Points
Elevated-risk surgery (intraperitoneal, intrathoracic, suprainguinal vascular)	1
History of ischemic heart disease	1
History of congenital heart failure	1
History of cerebrovascular disease	1
Preoperative treatment with insulin	1
Preoperative creatinine >2 mg/dL	1

**Table 2. T2:** American Society of Anesthesiologist's Physical Status (ASA-PS) - ASA classification

ASA Classification	Definition
ASA I	Normal healthy patient
ASA II	Patient with mild systemic disease
ASA III	Patient with severe systemic disease
ASA IV	Patient with severe systemic disease that is constant threat to life
ASA V	Moribund patient not expected to survive without operation
ASA VI	Declared brain dead patient whose organs are being removed for donor purposes

The exclusion criteria will be age <50 years, surgery other than major abdominal, anesthesia other than general, RCRI <2 points, and ASA-PS other than 2, 3, or 4.

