Cardiovascular complications, mainly myocardial ischemia, left ventricular dysfunction, and arrhythmia—occur in one in seven patients older than 45 years within 30 days from an inpatient non-cardiac surgery [6]. Similarly, pulmonary complications are common—particularly after major abdominal surgery—with an estimated incidence of 9 to 40%. Atelectasis, pneumonia, and pulmonary aspiration are among the most common postoperative complications and can impact survival after surgery. Preoperative medical assessment prior to every major surgery has become the standard of care with objectives to assess the perioperative risk for morbidity and mortality, optimize the patient's medical condition, and mitigate the risk for cardiopulmonary complications and others [9]. A number of validated risk stratification tools, such as the Revised Cardiac Risk Index (RCRI), American University of Beirut (AUB)-HAS2 Cardiovascular Risk Index, the American Society of Anesthesiologist's Physical Status (ASA-PS), and the Gupta perioperative risk for myocardial infarction and cardiac arrest have been created and used to standardize and optimize the perioperative medical assessment process [10–12]. The utilization of point of care ultrasound (POCUS)—the application of portable ultrasound by clinicians at the bedside—has grown rapidly in the inpatient and outpatient settings and is a valuable tool that enhances the standard clinical assessment [13]. In particular, lung POCUS can reveal findings, such as mild pulmonary edema, atelectasis, fibrosis, or small pleural effusions, which can be subclinical and otherwise not detected by history and physical examination alone [14]. A structured approach to performing and evaluating lung POCUS has been highly useful. This was originally known as the lung ultrasound score, and was later refined by Dell'Aquila et al. as the integrated lung ultrasound score (iLUS) [15,16].

Studies conducted in the immediate preoperative period have shown that lung POCUS performed during anesthesiology evaluation can aid in determining fluid therapy and predicting major adverse cardiac events [17,18]. However, the specific role of POCUS beyond this immediate preoperative assessment of patients has not been studied adequately, especially in the clinic setting at the time of preoperative medical assessment [19].

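### The RCRI table behind the entry criterion lists congenital heart failure, apparently a slip for congestive; scored as printed, it would exclude some heart-failure patients and under-score others

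*Protocol article*

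**What the plan says.** In the protocol article, under Population, Inclusion and Exclusion Criteria, patients must "have RCRI ≥2 (moderate or higher risk), and ASA-PS: II, III, IV (Table 1 and 2"). The same section repeats the threshold as an exclusion: "RCRI <2 points, and ASA-PS other than 2, 3, or 4". Table 1 has six items worth one point each. The surgery item is "Elevated-risk surgery (intraperitoneal, intrathoracic, suprainguinal vascular"). The five clinical items are ischemic heart disease, heart failure, cerebrovascular disease, insulin treatment and creatinine above 2 mg/dL. The heart-failure item is worded "History of congenital heart failure". No footnote or other section defines it differently, and none of the other items gives a point for acquired heart failure.

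The Introduction lists the RCRI among validated risk stratification tools already in use. Nowhere does the article say that the index was adapted for this study. Methodology of Analysis uses RCRI twice more: as a covariate in the multivariate analysis and as a grouping variable for sensitivity analyses.

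**The concern.** Table 1 is the scoring that the entry criterion itself points to, so a wrong word in it is not confined to background text. The study enrols people "who undergo preoperative medical assessment for a major abdominal surgery under general anesthesia", aged 50 or over. Where that surgery is intraperitoneal it already earns one point, and a single further item then decides entry. An item restricted to congenital disease gives nothing to a patient with acquired heart failure.

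Two things would be at stake if staff used the printed wording. Some patients who meet the threshold on the index the protocol names would be turned away. Others would be enrolled with an RCRI one point too low, and that value would go into the model and the sensitivity groups. The restriction also sits oddly with the study's rationale. The Introduction argues that "lung POCUS can reveal findings, such as mild pulmonary edema, atelectasis, fibrosis, or small pleural effusions", so a score that ignores most heart failure is unlikely to be what was intended.

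**Working it through.** There is no sample-size, power or significance figure to reproduce. The check is a count of points against the cut-off.

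**Inputs**, all from Population, Inclusion and Exclusion Criteria and Table 1:
- Surgery item: S = 1 if intraperitoneal, intrathoracic or suprainguinal vascular, otherwise 0.
- Four clinical items unaffected by the wording (ischemic heart disease, cerebrovascular disease, insulin, creatinine above 2 mg/dL): 1 point each, with sum K from 0 to 4.
- Heart-failure item H for a patient with acquired heart failure: H = 0 as printed, H = 1 if the item covers heart failure in general.
- Eligible if RCRI = S + K + H is at least 2.

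**The single patient.** Intraperitoneal surgery, acquired heart failure, no other clinical factor (S = 1, K = 0):
- As printed: 1 + 0 + 0 = 1, below 2, excluded.
- Item covering heart failure in general: 1 + 0 + 1 = 2, eligible.

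**All clinical profiles.** Five yes/no clinical items give 2^5 = 32 profiles. Heart failure, where present, is taken to be acquired.

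| Surgery point | Eligible as printed | Eligible if any heart failure scores | Profiles that change |
|---|---|---|---|
| S = 1 | 30 of 32 | 31 of 32 | 1: heart failure alone |
| S = 0 | 22 of 32 | 26 of 32 | 4: heart failure plus exactly one other clinical item |

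The counts can be confirmed by hand.
- S = 1, as printed: a patient needs K of at least 1, which fails only for no factor and for heart failure alone, so 32 − 2 = 30. With the item widened, only the no-factor profile fails: 32 − 1 = 31.
- S = 0, as printed: a patient needs K of at least 2. That holds for 16 − 1 − 4 = 11 of the 16 combinations of the other four items, each with or without heart failure, so 2 × 11 = 22. With the item widened, a patient needs two of five items: 32 − 1 − 5 = 26.

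Without the surgery point, the patient with heart failure alone scores 0 as printed and 1 with the item widened, and is excluded either way.

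**Enrolled patients.** For anyone with acquired heart failure who enters through other items, the printed wording gives S + K in place of S + K + 1. The understatement is exactly one point.

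The table counts profiles, not patients. Turning it into patients would need the frequency of each profile among those screened, which the article does not give.

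**The case against.** The strongest reply is that this is a typographical slip with no shown effect. The criterion names a well-known index; the reference to Table 1 is a parenthesis. Internal medicine physicians who use the RCRI in routine assessment would probably score it from familiarity or from a standard form. Methodology of Analysis says only RCRI, without pointing back to Table 1. And nothing in the article spells out the index's heart-failure item, so the intended word cannot be proved from the text.

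Much of this stands. A reader might infer from the table that heart-failure patients are in fact being excluded and that the covariate is misclassified. The article does not support that, because it does not say what staff score from. A reader might also apply an assumed share to the planned 120 participants to get a number lost. No prevalence is given to support such a share. Besides, 120 is the enrolment target, so screening out candidates would change case mix and recruitment time rather than subtract from the 120. Nor does the article give any figure showing that the iLUS range would narrow.

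The reply does not remove the point. The printed wording and its scoring effect are both in the article and need no outside source. That the word is a slip is an inference, but one drawn from the text: a tool called validated, no declared change to it, and no point anywhere for acquired heart failure. The request is therefore to reconcile the item with the named index, which does not depend on proving the intended word.

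**Conclusion.** The point holds as an error in the definition of an eligibility item, with a conditional consequence. Scored as printed, the table moves a patient with intraperitoneal surgery and acquired heart failure alone from 2 to 1, and so from eligible to excluded. It also lowers RCRI by one point for any enrolled patient with acquired heart failure. With the surgery point, this changes eligibility for one of 32 clinical profiles.

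This rests on two assumptions. One is that staff score from the printed wording, which the article neither states nor rules out. The other is that the surgery earns its point, as intraperitoneal surgery does. The number of patients affected cannot be estimated from the document. The wording deserves correction because it sits inside the entry criterion and two sites work from it, not because harm has been shown.

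**What to change.** 1. Reconcile the heart-failure item in Table 1 with the validated RCRI that the protocol names, and use that one definition for screening, the model covariate and the sensitivity groups.
2. Confirm which wording the screening forms carry at the Jacobi and Laikon sites.
3. Only if the printed wording was used, re-score the patients already screened and report how many changed score or eligibility. If the forms carry the index's own wording, correcting the table is enough.

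The cost is a one-word correction and a small records check. Sample size, endpoints and analysis methods are untouched.

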### Intervention

Included patients will undergo lung POCUS examination as part of their preoperative medical assessment prior to surgery. This is typically performed by an internal medicine specialist, and is usually done in a week to a few days in an outpatient clinic (in case of elective surgeries), and inpatient 0-1 days prior (in case of urgent surgeries). The studies will be performed by a sole operator (author LP), who was trained in POCUS during his internal medicine residency program, has attended POCUS courses via the American College of Physicians, and has been using POCUS on a daily basis in his clinical practice for more than five years. A single operator was chosen to eliminate the impact of inter-operator variability. POCUS images will be saved. To validate the findings, the operator's interpretation will be confirmed by an independent reviewer, who is a POCUS-trained critical care attending physician at NYC H+H/Jacobi (author PG). Clinicians will be blinded to lung POCUS findings, which is in-line with the high-quality POCUS literature [18]. Exceptions will include POCUS findings that are considered by the operator as critical, such as possible lung collapse, severe pulmonary edema, or large pericardial effusion, which will be reported to the clinicians.

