A commercial handheld device will be used on its lung preset. The 12-zone lung POCUS examination will be performed (Figure 1). The iLUS will be calculated for every patient. The external lung fields will be examined dividing the surface of the thorax into 12 zones: 6 on the right (anterior: upper R1 and lower R2; lateral: upper R3 and lower R4; posterior: upper R5 and lower R6) and 6 on the left side (anterior: upper L1 and lower L2; lateral: upper L3 and lower L4; posterior: upper L5 and lower L6) (Figure 1). iLUS assigns 0 points to A-lines or?<2 separate B-lines plus regular sliding; 1 point with B-lines?≥3 or spaced focal points plus regular sliding; 2 points with coalescing B-lines, and 3 points to pulmonary consolidations with a score ranging from 0 (normal lungs) to 36 (worst case scenario). iLUS evaluation then integrates four additional parameters: i) presence of pleural effusion (value 0 if absent, value 1 if present), ii) presence of pericardial effusions (value 0 absent, value 1 present), iii) measurement of the inferior vena cava (IVC) respiratory variation (<33%) (value 0 if absent, value 1 if present), iv) diaphragm excursion. This last parameter will be measured during normal breathing via a right subcostal scan. An excursion?>2?±?0.5 cm will be considered normal (value 0 if absent), while a value below will be abnormal (value 1 if present). Therefore, the total value of the iLUS will be 40 (Table 3) [15].

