### Primary and Secondary Endpoints

The primary endpoint will be the composite of failure of extubation after surgery completion in the operation room with the need for re-intubation, unplanned use of continuous positive airway pressure (CPAP), bilevel positive airway pressure (BiPAP), or high-flow nasal cannula (HFNC) after postoperative extubation, admission to the intensive care unit for a primary cardiopulmonary etiology in the index admission, death from a primary cardiopulmonary etiology within 30 days from operation, or readmission for a primary cardiopulmonary etiology within 30 days from operation (whichever happens first). The secondary endpoints will be the individual components of the primary endpoint as above, the length of stay for patients discharged alive, the need for supplemental oxygen on post-operation day 1 in the surgery floor and the need for additional diagnostic tests or other interventions prior to the planned surgery as a response to critical POCUS findings. Length of stay is defined as the number of days from the day of the operation to the day when the patient is declared medically appropriate for discharge by the primary team.

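### The day-1 oxygen endpoint counts patients who were already on oxygen before surgery, and neither eligibility nor adjustment separates them out

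*Protocol article*

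**What the plan says.** Under Primary and Secondary Endpoints, the protocol article lists "the need for supplemental oxygen on post-operation day 1 in the surgery floor" as a secondary endpoint. It does not refer to the patient's oxygen use before surgery. In the same section, the ventilatory-support component of the primary endpoint is qualified: "unplanned use of continuous positive airway pressure (CPAP), bilevel positive airway pressure (BiPAP), or high-flow nasal cannula (HFNC) after postoperative extubation".

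Under Population, Inclusion and Exclusion Criteria, the exclusions are the mirror image of the inclusions: "The exclusion criteria will be age <50 years, surgery other than major abdominal, anesthesia other than general, RCRI <2 points", and then ASA-PS class. Patients qualify if they "have RCRI ≥2 (moderate or higher risk), and ASA-PS: II, III, IV". Under Intervention, the scan takes place in an outpatient clinic before elective surgery, or "inpatient 0-1 days prior (in case of urgent surgeries".

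Under Methodology of Analysis, the multivariable model contains iLUS class, age, sex, BMI, RCRI, ASA-PS, AUB-HAS-2, time from scan to surgery, and urgency. Oxygen or respiratory support at the scan is not among them.

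**The concern.** A patient on home oxygen, or an inpatient receiving oxygen at the scan, will usually still need it on the day after the operation. As worded, that patient is an event even if nothing has changed.

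This would only add noise if oxygen users were spread evenly over the iLUS classes, but they probably are not. The score rises with B-lines, consolidation and effusion, and the conditions that produce these findings also lead to oxygen use. The endpoint would then partly measure disease present at the scan, and an association with iLUS would partly restate it.

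That matters for the study's purpose. The Introduction argues for lung ultrasound because it can show disease that history and examination miss. A patient already on oxygen needs no scan to be recognised as having lung disease, so counting such patients as events flatters the score.

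**Working it through.** **No figure in the plan to reproduce.** The target of 120 patients is stated without an event rate for this endpoint. What follows is an illustration, not a correction of a stated number.

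**Step 1: which endpoints can already be met at the scan?**

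- Failed extubation with re-intubation: follows the operation, so no.
- Unplanned CPAP, BiPAP or HFNC after postoperative extubation: no.
- Cardiopulmonary death or readmission within 30 days of operation: no.
- Oxygen on day 1: the date is postoperative, but the state can be carried over unchanged, so yes.

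**Step 2: simple illustration.** Assumptions, none from the documents: 60 patients per iLUS class; true risk of new oxygen 20% in both classes; a share b of each class already on oxygen, all of whom count as events.

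Counted risk = b + (1 − b) × 0.20

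- b = 10% (high iLUS): 0.10 + 0.90 × 0.20 = 28.0%
- b = 2% (low iLUS): 0.02 + 0.98 × 0.20 = 21.6%
- Difference 6.4 points; odds ratio (0.280/0.720)/(0.216/0.784) = 1.41

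With b = 5% and 1%: 24.0% and 20.8%; difference 3.2 points; odds ratio (0.240/0.760)/(0.208/0.792) = 1.20. The true odds ratio is 1.0 in both cases.

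**Step 3: chance of a falsely significant result.** The p ≤ 0.05 threshold is taken as two-sided; the protocol does not say. For 28.0% against 21.6%, the standard error is √(0.280 × 0.720/60 + 0.216 × 0.784/60) = 0.0786. Then 0.064/0.0786 = 0.81, and Φ(0.81 − 1.96) is about 12.5%, against 2.5% in that direction without bias. For 24.0% against 20.8%, the standard error is 0.0761, the ratio is 0.42, and the chance is about 6%.

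**Step 4: wider range.** Let f be the share of all 120 patients on oxygen at the scan, h the fraction of them with high iLUS, and p the risk in everyone else, who are split evenly by iLUS with no true association.

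- High-iLUS risk = [(1 − f) × 0.5p + fh] / [(1 − f) × 0.5 + fh]
- Low-iLUS risk = [(1 − f) × 0.5p + f(1 − h)] / [(1 − f) × 0.5 + f(1 − h)]

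Example with f = 5%, h = 80%, p = 20%: 0.135/0.515 = 26.2% against 0.105/0.485 = 21.6%, a risk ratio of 1.21.

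The values 9% and 40% for p are the Introduction's range for pulmonary complications, borrowed because no day-1 oxygen rate is given. Each cell shows the spurious risk ratio for h = 80% to 100%, with the chance of a false positive in that direction in brackets.

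| p | f = 3% | f = 5% | f = 10% |
|---|---|---|---|
| 9% | 1.31–1.59 (7.7–14.3%) | 1.48–1.96 (12.7–27.8%) | 1.77–2.84 (28.4–65.8%) |
| 20% | 1.13–1.23 (5.5–8.8%) | 1.21–1.38 (8.4–16.0%) | 1.37–1.73 (18.0–42.1%) |
| 40% | 1.05–1.09 (4.2–5.8%) | 1.08–1.14 (5.7–9.1%) | 1.15–1.27 (10.6–22.0%) |

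If oxygen users are spread evenly (h = 50%), the risk ratio is 1.0 and the bias vanishes.

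**Step 5: after redefinition.** If oxygen users have the same 20% risk of needing more than their baseline, the counted risk is b × 0.20 + (1 − b) × 0.20 = 20% in both classes, and the odds ratio is 1.0. The overall event rate in Step 2 falls from 24.8% to 20% (or from 22.4% to 20%).

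**The case against.** The strongest reply is that this is operational detail. A condensed article may leave the meaning of a new need, and the list of baseline fields, to the full protocol or case report form. Broad entry is deliberate, since the Strengths section describes a pragmatic real-world study. The model adjusts for ASA-PS and urgency, and one sensitivity analysis drops patients with critical scan findings. With about 60 per class, a 6.4-point shift is smaller than its standard error.

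Much of this stands, and it keeps the point small. It does not remove it. The article qualifies the neighbouring ventilatory-support component as unplanned but leaves oxygen unqualified. ASA-PS is a broad grade, and RCRI as tabulated has no lung item. A stable home-oxygen user need not have a critical finding. The small sample makes a false positive less likely, but it does not move the estimate back to the null.

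Stronger readings are tempting, and the documents do not support them:

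- *That such patients already have the primary outcome.* The components in Step 1 are tied to the period after surgery. Severe lung disease beforehand raises their risk, but that is prediction, not a prevalent outcome. The intensive-care component is worded by index admission, but the Abstract sets the outcome period as the 30 days after surgery, so it is not counted here.
- *That intubated patients will be enrolled in numbers.* "Verbal informed consent will be obtained from all participants", which makes this unlikely.
- *That iLUS cannot be scored in these patients.* Patients on plain oxygen breathe spontaneously. Only the diaphragm item is tied to unassisted breathing ("This last parameter will be measured during normal breathing via a right subcostal scan"), and it is 1 point of 40. No breathing mode is stated for the vena cava item.
- *That oxygen users should be excluded.* That would narrow a deliberately broad population to solve a problem of endpoint wording.

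**Conclusion.** The point holds for one secondary endpoint. As worded, day-1 oxygen can be met without any postoperative change, and nothing in the stated eligibility or adjustment corrects for that. The direction of bias, towards an apparent association with iLUS, rests on the plausible assumption that oxygen users cluster in the higher iLUS class.

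Its size depends on the share of oxygen users, which the documents do not give. The odds ratio is about 1.2 to 1.4 in the simple illustration. Across the wider range, the risk ratio runs from 1.05 to 2.84, largest where oxygen users are common and the background rate is low. These figures must not be carried over to the primary composite. This is a cheap improvement to a definition, not a flaw in the study's main comparison.

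**What to change.** Record oxygen use and any respiratory support, with its level, at the scan visit. Define the secondary endpoint as a new requirement for supplemental oxygen on postoperative day 1, or an increase over that recorded baseline. Leave the eligibility criteria as they are.

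The cost is one extra baseline field, a sentence in the endpoint definition, and a slightly lower day-1 oxygen event rate.
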